## Abstract

The herbal medicine Yukgunja-tang has been widely used for the treatment of functional dyspepsia (FD) in the clinical setting of East Asian traditional medicine. This paper presents a protocol for a randomized, assessor-blind, controlled, multicenter, three-arm parallel clinical trial comparing the effectiveness, safety, and cost-effectiveness of Yukgunja-tang with Pyeongwi-san and usual care. A total of 140 participants with Rome IV-diagnosed FD will be randomly assigned to either the Yukgunja-tang (n = 56), Pyeongwi-san (n = 56), or usual care (n = 28) groups. All participants will be educated on dietary guidelines for FD patients. Participants in the Yukgunja-tang and Pyeongwi-san groups will take investigational products for 6 weeks. All participants will be assessed for clinical parameters at weeks 0, 3, 6, 9, and 24. The primary outcome will be measured on the total dyspepsia symptom scale, and the secondary outcome will include the single dyspepsia symptom scale, overall treatment effect, the visual analog scale for dyspepsia, FD-related quality of life, hospital anxiety and depression scale, EuroQol-5 dimension, pattern identification, and serum levels of acyl-ghrelin and deacyl-ghrelin. Adverse events and laboratory tests will be monitored for safety assessment. The results will provide evidence of the effectiveness, safety, and cost-effectiveness of Yukgunja-tang in the treatment of FD.

## 1. Introduction

Functional dyspepsia (FD) is a chronic non-communicable gastrointestinal disease characterized by the following various symptoms: postprandial fullness, early satiety, and epigastric pain or burning without evidence of structural abnormality [1]. The prevalence of FD is 5–11% worldwide [2], and 7.7% in Korea [3]. More than 50% of patients with FD report that it interferes with their daily life, and thus it is a disease of great socioeconomic burden [4]. In Western medicine, various drugs are used to relieve the symptoms of indigestion. However, there are limitations to conventional treatment for treating various symptoms of FD, and the demand for complementary and integrative medicine is increasing globally [5].

Herbal medicine, one of the complementary and integrative forms of medicine, has been widely used for the treatment of various diseases, including FD, worldwide [6,7]. Because herbal medicines are typical multitarget multicomponent agents [8], they have promising potential for the treatment of FD, which shows various pathological mechanisms and symptoms. According to the statistical data of the Korea Health Insurance Review and Assessment Service, FD ranked 8th among outpatients at Korean medical institutions in 2021, and many people are receiving Korean medicine treatment such as herbal medicine and acupuncture for FD [9].

Yukgunja-tang (YGJ; Rikkunshito in Japanese, Liujunzi-tang in Chinese), one of the representative herbal medicines used to treat FD, is an herbal prescription consisting of eight herbs: Pinelliae Tuber, Citri Unshius Pericarpium, Ginseng Radix, Atractylodis Rhizoma Alba, Poria Sclerotium, Glycyrrhizae Radix et Rhizoma, Zingiberis Rhizoma Recens, and Zizyphi Fructus. In particular, according to a survey conducted on 349 clinical Korean medicine doctors in 2017, YGJ was the most frequently used herbal prescription among noninsured herbal medicines in Korea [10]. However, despite its active use, YGJ is not covered by health insurance in Korea, causing a burden on one’s private medical expenses.

In addition, although several clinical studies of YGJ for the treatment of FD have already been carried out in other East Asian countries, including Japan and China [11,12,13,14], there is no large-scale clinical trial to investigate the effectiveness of YGJ on FD, reflecting the Korean medicine clinical field. According to a recent systematic review, the administration of YGJ, alone or in collaboration with Western medicine, can be an effective and safe treatment option for FD [15]. However, the authors concluded that there was uncertain evidence due to the low quality of included studies [15]. Therefore, a well-designed, high-quality randomized controlled trial (RCT) is needed to verify the effectiveness of YGJ in the treatment of FD.

In this study, we aimed to evaluate the therapeutic effect of YGJ on FD by comparing it with the usual care control group. In addition, we will compare the effectiveness of YGJ with that of Pyeongwi-san (PWS). PWS, an herbal medicine that is commonly used for the treatment of FD, has been shown to be effective in the treatment of FD through previous clinical trials [16,17]. Furthermore, it is the most frequently used herbal medicine in Korea for the treatment of FD within the scope of national health insurance [7], and is therefore an appropriate control group to evaluate the noninferiority and cost-effectiveness of a specific herbal medicine for the treatment of FD. We aimed to analyze the noninferiority and cost-effectiveness of YGJ compared with PWS, exploring the possibilities of YGJ being listed for insurance coverage in Korea. To our knowledge, this study is the first to test the noninferiority and cost-effectiveness of YGJ, which is actively used for FD treatment in clinical settings.

## 2. Methods

### 2.1. Study Design

A randomized, assessor-blind, three-arm, parallel-group, multicenter clinical trial will be conducted at the Kyung Hee University Korean Medicine Hospital, Daejeon Korean Medicine Hospital of Daejeon University, and Semyung University Korean Medicine Hospital in the Republic of Korea from June 2022 to December 2023. The trial includes 6 weeks of medication or usual care (week 0 to 6) and a follow-up of 18 weeks (from week 6 to 24), following 2 weeks of a run-in period after the screening visit (Table 1 and Figure 1). It will be performed according to the declaration of Helsinki and good clinical practice guidelines. Investigators will provide detailed trial information to participants through standardized interviews prior to participation, and they will obtain written informed consent from all participants. The participants will be allowed to withdraw from the study at any time without penalties. We report this protocol in accordance with the standard protocol items: the recommendations for interventional trials 2013 statement [18].

### 2.2. Participant Recruitment

We will recruit participants through offline and online recruitment advertisements, including posting posters on bulletin boards and websites of trial institutions. If participant registration is delayed, local advertisements in local public transportation and newspapers will be placed.

### 2.3. Inclusion Criteria

Adults aged 19–75 years at the time of screening visit;Diagnosed with FD according to Rome IV criteria (having one or more symptoms of postprandial fullness, early satiety, epigastric pain, and epigastric burning without organic findings, occurred at least 6 months ago and persisted for at least past 3 months);The intensity of dyspeptic symptoms measured by a 0–100 mm visual analog scale (VAS) is at least 40 points; andVoluntarily signed written informed consent approved by the institutional review board (IRB).

### 2.4. Exclusion Criteria

Diagnosed with specific diseases, including peptic ulcer, esophageal cancer, MALT lymph cancer, stomach cancer, colon cancer, biliary tract and pancreatic diseases (except asymptomatic cholelithiasis), and inflammatory bowel disease within 1 year prior to the screening visit;Having more severe symptoms of reflux esophagitis and irritable bowel syndrome than those of dyspepsia (Participants with reflux esophagitis or irritable bowel syndrome can participate in this clinical trial. However, through the participants’ interview and medical history taking, participants whose symptoms of reflux esophagitis (including reflux and heartburn) and irritable bowel syndrome (including abdominal pain or discomfort related to the pattern of defecation) are more severe than those of dyspepsia are excluded.);Having alarming symptoms such as severe weight loss, bloody stool, dysphagia, swallowing pain, and persistent vomiting;Diagnosed with mental disorders, such as major depressive disorder, anxiety disorder, and panic disorder, or having a depression score of 11 or higher on the Hospital Anxiety and Depression Scale (HADS) at the screening visit;Having serious systemic diseases in heart, lung, liver, or kidney, or presence of other malignant diseases;Having a history of gastrointestinal surgery (except for appendectomy more than 6 months ago);Taking medications that can affect the gastrointestinal tract, including proton pump inhibitors, histamine receptor antagonists, antacids, prokinetics, antidepressants, gastric fundus relaxants, gastric mucosal protectants, nonsteroidal anti-inflammatory drugs, anticholinergics, or oral corticosteroids, or receiving *Helicobacter pylori* eradication treatment, within 2 weeks prior to the screening visit (taking low-dose aspirin (100 mg/day or less) for the purpose of preventing cardiovascular disease is allowed);Having received Korean medicine treatments such as acupuncture, herbal medicine, or moxibustion for the purpose of improving dyspeptic symptoms within 2 weeks prior to the screening visit, or who are planning to receive them during the trial period;Having severe liver or renal diseases (aspartate aminotransferase or alanine aminotransferase levels ≥ 3 times the upper limit of normal levels or creatinine levels ≥ 2 times the upper limit of normal levels);Having a history of alcohol or drug abuse;Women who are pregnant or lactating, or women who do not agree to use effective methods of contraception during the clinical trial;Having genetic problems, such as galactose intolerance, Lapp lactase deficiency, or glucose-galactose malabsorption;Having known hypersensitivity to investigational products (according to the Korean Ministry of Food and Drug Safety (KMFDS), adverse events such as pseudoaldosteronism, myopathy, and skin reactions (rash, redness, itching, hives) may occur after the administration of YGJ and PWS.);Having taken other investigational products within 3 months; andHaving judged to be unsuitable for participation in this trial by investigators.

### 2.5. Dropout and Early Termination Criteria

At any time during the clinical trial, participants can voluntarily withdraw from the clinical trial. Additionally, anyone who meets any of the following conditions will be removed from the trial at the discretion of investigators.

Found to violate the inclusion and exclusion criteria after screening visit;In the case where the participant requests discontinuation of the trial or refuses the treatment due to unsatisfactory treatment effects during the trial period;In the case where the participant cannot be tracked during the trial period;When it is judged by investigators that trial participation is no longer possible due to an adverse reaction or a concomitant disease;In the case of taking prohibited drugs that may affect the trial result without the instruction of investigators during the trial period;When it is judged that the effect evaluation of the clinical trial is not appropriate because the overall compliance with the investigational products is less than 70% in YGJ and PWS groups;When the participant violates the trial plan, and it is difficult for the participant to continue the trial; andWhen investigators judged that the progress of the clinical trial is no more appropriate.

In principle, this clinical trial will be finalized when the registration of the planned number of participants is completed and the completeness of the collected data is secured. However, this clinical trial can be discontinued in the following cases: (1) if the supplied investigational products are found to be harmful, (2) if moderate or severe adverse events judged to be related to the investigational products occur in more than 25% of all participants, and (3) in the case when the targeted number of participants is not registered even though a sufficient recruitment period has been given.

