### 2.11. Statistical Analysis

A statistician independent of the trial procedure and assessment will conduct statistical analysis using SAS^®^ Version 9.4 software (SAS Institute Inc., Cary, NC, USA). In principle, for effectiveness analysis, a full analysis set of all randomly assigned participants who are evaluated at least once after receiving a prescription of investigational products at least once will be conducted, according to intention-to-treat analysis. If necessary, per-protocol set (PPS) analysis will be performed, including participants who have completed the entire process of the clinical trial and have no significant violations affecting the test results. Participants with less than 70% compliance with the investigational product, taking prohibited drugs for the treatment and management of diseases other than gastrointestinal disease under the judgment of investigators, or experiencing events that can cause digestive symptoms such as sudden stress during the clinical trial period, will be excluded from the PPS analysis. Safety analysis will include all data obtained from participants who have taken at least one investigational product in the YGJ and PWS groups and all participants in the usual care group.

The demographic characteristics of participants will be summarized by group. Continuous data will be presented as mean and 95% confidence intervals (CIs), whereas dichotomous data will be displayed as frequency and percentage. The primary outcome of this study is the difference in the TDS score at week 6 between the YGJ and usual care groups (Hypothesis 1).

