### 2.12. Economic Evaluation

We will conduct an economic evaluation along with the RCT for effectiveness and safety. We will estimate the cost-effectiveness of YGJ compared with PWS or usual care from the health care system and societal perspective. Costs will consist of medical costs, nonmedical costs (transportation costs, time costs, and care costs), and costs associated with productivity loss using the Work Productivity and Activity Impairment Questionnaire: General Health V2.0, which is the most frequently used instrument for measuring productivity loss in Korea [30,31]. Cost data will be obtained from each participant using a separately developed cost questionnaire and institutional data at all visits except at the screening visit. However, if necessary, data from Statistics Korea can be used. Effectiveness data will be collected from the main RCT. Utility data will be collected from the main RCT using the EQ-5D-5L questionnaire, and quality-adjusted life years gained will be calculated using the area under the curve method [25]. We will investigate the cost and effectiveness data of TDS, OTE, and EQ-5D-5L for economic evaluation through telephone follow-up at week 24, even after the end of the 9-week clinical trial for effectiveness and safety evaluation of YGJ. These effectiveness, utility, and cost data will be used to calculate the incremental cost-effectiveness (cost–utility) ratio between the YGJ and the control groups at each visit. If necessary, we will perform a one-way sensitivity analysis on possible variables and present a tornado diagram, and also perform a probability sensitivity analysis using the distribution and representative values of the variables. In addition, subgroup analysis will be conducted according to the RCT subgroup analysis plan of the effectiveness outcome measures. Among the dropout criteria of the clinical trial for effectiveness evaluation, if the investigator judges that it is no longer possible for a participant to participate in the trial due to an adverse reaction or comorbid disease in the clinical trial process, participants will not be excluded from the data collection of the economic evaluation, and a telephone follow-up survey will be performed at week 24 with the consent of the participants. If we cannot observe the full yield cost and effectiveness outcomes of interventions during the 6 months clinical trial period, we will develop a decision-analytic model and conduct a long-term evaluation by secondary analysis.

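### Section 2.5 does not separate stopping product from leaving the trial, and only one kind of removed participant keeps any later follow-up

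*Protocol article*

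**What the plan says.** Protocol article, section 2.5, introduces its list of conditions with the rule that "anyone who meets any of the following conditions will be removed from the trial at the discretion of investigators". What ends is participation in the trial. The section has no separate provision for stopping product while staying under observation. Four of the listed grounds matter here:

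- late-found ineligibility: "Found to violate the inclusion and exclusion criteria after screening visit"
- dissatisfaction, where the participant "requests discontinuation of the trial or refuses the treatment due to unsatisfactory treatment effects during the trial period"
- "In the case of taking prohibited drugs that may affect the trial result without the instruction of investigators during the trial period"
- a judgement that the effect can no longer be properly evaluated because "the overall compliance with the investigational products is less than 70% in YGJ and PWS groups"

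Section 2.12 makes one exception, for people whose participation has become impossible: "due to an adverse reaction or comorbid disease in the clinical trial process, participants will not be excluded from the data collection". This concerns economic data only, and the week-24 telephone survey goes ahead if they agree. No other ground in section 2.5 has such an exception.

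Section 2.11 analyses a full analysis set (FAS) "according to intention-to-treat analysis". It needs at least one evaluation after prescription. Compliance under 70% appears again there as an exclusion from the per-protocol set (PPS), which is to be analysed only if needed. The primary model is an MMRM over visits.

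**The concern.** When removal from the trial also ends measurement, the reason for removal becomes the reason the data are missing. Leaving because treatment is not working is directly linked to response. Taking a prohibited antacid, acid suppressant or prokinetic plausibly is too. Low compliance is linked to adherence and can arise only in the YGJ and PWS arms. The people who apply the list can know the allocation: under section 2.6 an investigator opens the envelope in front of the participant, and under section 2.7 only the outcome assessor is blind.

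Two results are at stake. One is the week-6 TDS comparison behind Hypotheses 1 to 3, including the noninferiority margin, which section 2.11 takes from the confidence interval of Hypothesis 2. The other is the cost-effectiveness result, which would lose later cost and utility data from people whose treatment failed or who turned to other drugs.

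**Working it through.** **1. Does removal end data collection?** Section 2.5 speaks of removal from the trial. Section 2.12 has to state that one group of leavers is not excluded from economic data collection. That statement is needed only if removed participants are otherwise excluded. The implication is reasonable, though the article does not spell it out for the other grounds.

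**2. What is lost, by time of removal** (visits from Table 1, FAS definition from section 2.11):

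| Removed | In FAS? | Week-6 TDS | Later data |
|---|---|---|---|
| Before Visit 3 (week 3) | No, no post-baseline evaluation | Missing | Missing |
| Between Visits 3 and 4 | Yes | Missing | Missing |
| At or after Visit 4 (week 6) | Yes | Present | Week 9 and/or 24 missing |

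Section 2.8 counts remaining product at Visits 3 and 4, so overall compliance is complete only at Visit 4, when the week-6 TDS is also taken. The compliance ground therefore falls mainly in the last row. Dissatisfaction, prohibited drugs and late-found ineligibility can fall in any row.

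**3. The plan's own figures** (section 2.10: difference 2.70, SD 3.65, 5% two-sided, 80% power, ratio 2:1, 20% dropout).

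- Usual care n = (1.96 + 0.8416)² × 3.65² × (1 + 1/2) / 2.70² = 21.5, rounded up to 22. YGJ = 44. Both reproduce.
- With dropout: 22/0.8 = 27.5, giving 28. 44/0.8 = 55, taken as 56 to keep 2:1. The total of 140 reproduces.
- The allowance is 0.20 × 56 = 11.2 in each herbal arm and 0.20 × 28 = 5.6 in usual care, or 28 of 140. It protects precision and does nothing about bias.
- By the noncentral t, power is 79.7% at 44:22. It would be 88.5% if all 56 and 28 were measured at week 6 and the effect were undiluted.

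**4. Illustration for Hypothesis 1.** Let m be the share of an arm removed for reasons the observed data do not explain, and g the points by which their true week-6 improvement falls short of what the model predicts. The arm mean is then overstated by m × g, and the difference shifts by (m_YGJ − m_UC) × g. Neither m nor g is in the article. I take g from half the assumed effect (1.35) to one SD (3.65), and a net difference in m of up to 0.20 either way.

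- m_YGJ − m_UC = +0.20: 0.20 × 1.35 = 0.27 to 0.20 × 3.65 = 0.73 points overstated.
- m_YGJ − m_UC = 0.10 − 0.30 = −0.20: 0.27 to 0.73 points understated.
- Relative to 2.70: 0.27/2.70 = 10% and 0.73/2.70 = 27%.

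**5. Hypothesis 3.** Score change as improvement, hold interval widths fixed, and write b1, b2, b3 for the biases in the YGJ, usual care and PWS means. The margin moves by b3 − b2 and the PWS-minus-YGJ contrast by b3 − b1. The room between them moves by (b3 − b2) − (b3 − b1) = b1 − b2. The noninferiority decision is therefore exposed to the same shift as Hypothesis 1.

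**6. Cost.** If each unfollowed leaver costs C more than a retained participant after removal, a retained-only incremental cost (YGJ minus usual care) is wrong by (m_UC − m_YGJ) × C. With assumed rates of 30% and 10% this is 0.20 × C. The article gives no value for C.

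**The case against.** A reader might infer more than the article supports. Four stronger readings are tempting.

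- **That section 2.5 contradicts the intention-to-treat analysis.** It does not delete data already collected. Anyone evaluated once stays in the FAS, and naming low compliance as a PPS exclusion presumes that such people remain in the FAS. What stands is that their later outcomes go unmeasured, which weakens the intended analysis.
- **That the arm-specific compliance rule biases week 6.** It probably costs little week-6 data, because overall compliance is complete only at Visit 4. Removal is also conditional on judgement.
- **That MMRM cannot handle these losses.** It handles dropout explained by observed scores, such as leaving after a poor week-3 TDS. Late-found ineligibility need not be related to outcome at all. What stands is that removal driven by what happens after the last visit, or decided with knowledge of the arm, may not be missing at random.
- **That the bias favours YGJ.** The sign depends on which arm loses more non-responders. Usual care offers dietary guidance alone, so it could be that arm. The 20% allowance also covers withdrawal, loss to follow-up and adverse events, so treating all of it as informative is an upper illustration.

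On cost, section 2.12 and Table 1 collect cost and EQ-5D-5L data at every visit after screening, so data up to removal exist. The loss is of later data. People who refuse contact or cannot be traced are lost under any rule.

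**Conclusion.** The point holds as a design weakness that the article itself states, not as detail left to a fuller document. Section 2.5 merges stopping product with leaving the trial, on grounds partly linked to response and adherence, at the discretion of investigators who can know the arm. The single exception in section 2.12 implies that other removed participants are lost to later collection. Hypotheses 1 to 3 and the margin then depend on a missing-at-random assumption that may fail, and the economic analysis loses later data from dissatisfied leavers and users of prohibited drugs.

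The extent of removal is unknown because it is discretionary, and the article does not determine the size or direction of the bias. The shift of up to 0.27 to 0.73 points in either direction rests on an assumed net difference of up to 20% in informative removal and an assumed gap of 1.35 to 3.65 points. It shows scale and is not an estimate. The change is cheap enough that it should be made.

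**What to change.** State in section 2.5 that meeting a listed condition does not end outcome collection. Everyone randomized who has not withdrawn consent to follow-up and can be reached keeps the scheduled TDS, cost and EQ-5D-5L assessments, by telephone if needed, and stays in the FAS.

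Handle eligibility, compliance and prohibited-drug violations through the PPS. Name dyspepsia drugs there explicitly, because the specific prohibited-drug exclusion in section 2.11 covers only drugs for non-gastrointestinal disease. Report the PPS alongside the FAS for Hypothesis 3 as a matter of course, since TDS measured after prohibited drugs may pull YGJ and PWS together.

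Extend the week-24 call in section 2.12 to every early leaver who consents.

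None of this changes when product is stopped. The cost is a protocol amendment, consent wording, and contact with at most about 28 participants (20% of 140) at time points already scheduled. The statistical price is possible dilution of the effect from TDS measured after prohibited drugs.

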### 2.8. Interventions

Participants will be randomly assigned to receive YGJ, PWS, or usual care for 6 weeks. All investigational drugs in the YGJ and PWS groups were manufactured by Kracie Pharma Korea Co., Ltd. (Seoul, Republic of Korea) and Hanpoong Pharm & Foods Co., Ltd. (Jeonju, Republic of Korea), respectively, in compliance with the Korean Good Manufacturing Practice guidelines.

YGJ (Kracie Yukgunja-tang Extract Fine Granule; product code: 201310401) is a light-brown-to-brown-colored fine granule, and participants will consume one pack (3.0 g) twice a day before or between meals for 6 weeks. The raw materials of YGJ extract per pack are Ginseng Radix 2 g; Atractylodis Rhizoma Alba 2 g; Poria Sclerotium 2 g; Pinelliae Tuber 2 g; Citri Unshius Pericarpium 1 g; Zizyphi Fructus 1 g; Zingiberis Rhizoma Recens 0.25 g; and Glycyrrhizae Radix et Rhizoma 0.5 g. PWS (Hanpoong Pyeongwi-san, mixed single extract; product code: 200000079), an active control, is a brown-colored powder, and participants will consume one pack (2.18 g) three times a day before or between meals for 6 weeks. The component per 1 pack is a powder extract of Atractylodis Rhizoma 0.95 g; Citri Unshius Pericarpium 0.56 g; Magnoliae Cortex 0.10 g; Glycyrrhizae Radix et Rhizoma 0.20 g; Zingiberis Rhizoma Recens 0.03 g; and Zizyphi Fructus 0.34 g. All investigational products will be stored at room temperature, and a pharmacist will check their storage, dispensation, and quality. During the administration of the investigational products, investigators will check the number of remaining drugs to ensure that the participants have taken the drugs properly (Visits 3 and 4). Medication compliance (%) will be calculated by dividing the number of drugs actually taken by the number of drugs that should have been taken.

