During the clinical trial period, dietary guidelines based on dietary recommendations prepared for Korean dyspepsia patients [20] will be distributed and explained to all participants in the three groups. The usual care group will perform daily management while following the dietary guidelines distributed during the clinical trial period without administration of any investigational product. Under the judgement of the investigator, medications and treatments other than those prohibited in this clinical trial may be permitted, and all medications and treatments performed during the trial period should be recorded in the CRF. YGJ and PWS groups are also allowed to perform usual care.

Concomitant medications are permitted only if the investigators determine that they do not affect the outcomes of this study, including drugs used to treat underlying diseases or therapeutic drugs in case of adverse events. The investigators will check and record all the detailed information of concomitant medications in the CRF. During the entire trial period, participants are prohibited from taking medications, including proton pump inhibitors, histamine receptor antagonists, antacids, prokinetics, antidepressants, gastric fundus relaxants, gastric mucosal protectants, nonsteroidal anti-inflammatory drugs, anticholinergics, oral corticosteroids, and treatment regimens for *Helicobacter pylori*, which, in the opinion of the investigators, may affect the gastrointestinal tract. In addition, it is prohibited to receive Korean medicine treatments such as acupuncture, herbal medicine, or moxibustion for the purpose of improving indigestion during the clinical trial period.

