### 2.10. Sample Size Calculation

The primary objective of this study is to compare and evaluate the effectiveness of 6 weeks of administration of YGJ compared to usual care in participants with FD. We will test whether there is a difference in the degree of reduction in TDS scores between the two groups after 6 weeks through a superiority test. Based on the results of a previous study comparing YGJ and a placebo [19], and considering the 15% placebo effect, it is assumed that the difference between the average TDS change between the YGJ and usual care groups after 6 weeks is 2.70, and the standard deviation is 3.65. The significance level is 0.05, and the power is 80%. Taking into account the previous studies [11,19] and ethical issues, the ratio between the YGJ and usual care groups is assigned at 2:1. Therefore, 44 and 22 participants are required for the YGJ and usual care groups, respectively.

Additionally, the second purpose of this study is to evaluate the noninferiority of YGJ compared with that of PWS. For this, the noninferiority margin should be defined based on the results of the effect evaluation between the PWS and usual care groups. However, due to the lack of prior research and related data, we will first test the superiority of PWS compared to usual care after 6 weeks to define the noninferiority margin. Under the assumption that the effect size of the YGJ and PWS is the same, 44 participants are also required in the PWS group. Therefore, considering the 20% dropout rate, a total of 140 participants, including 56, 56, and 28 participants in the YGJ, PWS, and usual care groups, respectively, are required.

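### The 25% adverse-event stopping criterion counts against all participants, so one harmful product alone would have to exceed 62.5% of its arm to meet it

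*Protocol article*

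**What the plan says.** Section 2.5 lists three grounds for ending the trial early. The rule is permissive, and its first ground carries no figure: "this clinical trial can be discontinued in the following cases: (1) if the supplied investigational products are found to be harmful". The second is numerical: "if moderate or severe adverse events judged to be related to the investigational products occur in more than 25% of all participants". The third concerns failure to recruit. Criterion (2) is therefore the only safety ground with a threshold.

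Section 2.8 describes two products with different manufacturers, herbs and schedules. For YGJ, "participants will consume one pack (3.0 g) twice a day before or between meals for 6 weeks"; for PWS, "participants will consume one pack (2.18 g) three times a day before or between meals for 6 weeks". The same section has the usual care group manage their condition "without administration of any investigational product". Section 2.10 sets the arm sizes: "56, 56, and 28 participants in the YGJ, PWS, and usual care groups, respectively, are required".

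Section 2.11 shows that the authors restrict to exposed participants where they mean to. In the two herbal arms, the safety analysis covers "participants who have taken at least one investigational product in the YGJ and PWS groups".

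**The concern.** Only someone who takes YGJ or PWS can have an adverse event related to a product. The denominator of criterion (2) nevertheless includes the 28 of 140 who take none, and it adds the two products together. The rate that one product must reach before the criterion is met then depends on how well the other is tolerated and on an arm that cannot contribute events.

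If the two products behave alike, the dilution is mild. If one causes most of the events, the threshold for that product is far above the 25% that a reader sees. Any decision would then rest on the unquantified first ground and on judgement, with no figure to prompt a review.

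**Working it through.** **Inputs.** Allocation 2:2:1 (section 2.6); arms of 56, 56 and 28, total 140 (section 2.10); threshold above 25% of all participants (section 2.5). The arm sizes reproduce from the stated 44 and 22 evaluable participants with 20% dropout: 44/0.8 = 55, taken to 56 to keep 2:1; 22/0.8 = 27.5, taken to 28; 56 + 56 + 28 = 140. The article gives no operating figure for the 25% rule, so there is none to reproduce.

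**Effective threshold.** 0.25 × 140 = 35, so at least 36 participants must be affected.
- Both products equally harmful: 36/112 = 32.1% of the exposed (limit 35/112 = 31.25%).
- One product only: 36/56 = 64.3% of its arm (limit 35/56 = 62.5%).

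The 62.5% is 0.25 × 5/2, so it follows from the allocation ratio and holds at any stage with balanced enrolment. At half enrolment (28, 28 and 14), 0.25 × 70 = 17.5, so at least 18 are needed, and 18/28 = 64.3%.

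**Assumptions for the probabilities.** True rates are assumed. Arms are exactly balanced and independent, usual care has no product-related event, and each participant's event status is known when counted. Section 2.5 gives no schedule for looking at the count. I therefore use two looks for both rules so that they are compared on the same basis.

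**Present rule, two looks.** Let X1 and X2 be the affected counts in the first and second halves, each Bin(28, p1) + Bin(28, p2). Then P(met) = P(X1 ≥ 18) + P(X1 ≤ 17 and X1 + X2 ≥ 36).

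| True rates, one product / other | Met at first look | Met at either look | Single look at 140 only |
|---|---|---|---|
| 40% / 5% | 4.4% | 4.7% | 0.6% |
| 40% / 10% | 12.6% | 13.9% | 4.3% |
| 50% / 5% | 23.2% | 26.8% | 12.5% |
| 40% / 20% | 41.1% | 49.6% | 34.0% |
| 60% / 5% | 59.8% | 71.4% | 58.9% |
| 40% / 40% | 91.1% | 97.9% | 96.5% |

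**Per-product rule, looks at 28 and 56 dosed.** 0.25 × 28 = 7, so at least 8; 0.25 × 56 = 14, so at least 15. At a true 40%, the rule is met 92.6% of the time at the first look and 99.0% by the second.

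**Removing usual care alone.** 0.25 × 112 = 28, so at least 29 of the exposed. One product would still need 29/56 = 51.8% of its arm. At 40% / 5%, this version is met 20% of the time with a single look at full enrolment.

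**False prompts.** If both products share a true rate below 25% and the per-arm crossing probability is c, at least one crosses with probability 1 − (1 − c)².
- 10%: c = 0.0051, giving 1.0%.
- 15%: c = 0.0554, giving 11%.
- 20%: c = 0.2333, giving 41%.

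By the two-look formula above, the present rule gives less than 0.001%, 0.1% and 2.2% at the same rates.

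**The case against.** The strongest reply is that a single harmful product is already covered. Criterion (1) has no minimum rate and no pooled denominator. Investigators may remove an individual for an adverse reaction (2.5). They open the envelopes and know allocation (2.6), and monitors check adverse events on their visits (2.13). That stands. A reader might infer that the trial could not be stopped for one harmful product; the text does not support this. None of these safeguards supplies a figure, however, so they do not repair the one that is given.

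Second, the result depends on how often the count is examined. That also stands. On a running count from 50 enrolled, simulation gives about 14% at 40% / 5%, 47% at 50% / 5% and 68% at 40% / 20%. The 0.6% from a single look at the end is therefore the least favourable case, and a claim that the criterion would usually go unmet is too broad. It is met more often than not at 60% / 5%, even with one look.

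Third, such rates are remote. The Discussion reports no significant difference in adverse reactions between YGJ and placebo over 8 weeks and none related to a modified PWS. This lowers the priority. A stopping threshold exists for the unexpected case, though, and section 2.4 names pseudoaldosteronism and myopathy as possible.

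Fourth, a whole-trial denominator can be defended for a rule that ends the whole trial. It is a design choice, and it does not contradict the safety set in 2.11. The objection is to how it performs when only one product is at fault.

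**Conclusion.** The point holds as a low-priority improvement. The effective threshold of 62.5% for one product is arithmetic from the stated denominator and the 2:2:1 ratio, and needs no assumption beyond balanced enrolment and no product-related events in usual care. The probabilities rest on assumed rates and on two looks. Under those, the weakness is greatest at roughly 40–50% on one product with a low rate on the other, where the criterion is met about 5% to 27% of the time if the other product is at 5%. It fades as the second product's rate rises and is absent when both are at 40%.

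It would be wrong to conclude that participants are unprotected or that the safety results will be biased. Criterion (1), individual withdrawal and monitoring remain. The safety analysis uses its own population, and the primary comparison does not depend on this criterion.

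**What to change.** In 2.5, replace criterion (2) with a per-product version, for example: *a moderate or severe adverse event attributed to YGJ, or to PWS, has occurred in more than 25% of those who have taken at least one dose of that product, assessed when 28 and when 56 participants have taken it, each participant counting once.* Add that crossing leads to a safety review of that product by the investigators and the IRBs, with possible discontinuation of that arm, and does not by itself end the trial. The 25% and the review points are for the sponsor and the IRBs to settle.

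The cost is one or two sentences and an IRB-approved amendment recorded in the registry (2.15). No new data are needed: Table 1 already collects adverse events at Visits 2 to 5, and 2.11 already identifies who took a product. The downside is the higher rate of false prompts shown above. Two fixed reviews limit it: checking after every participant from 20 dosed would raise the 41% at a true 20% to 69%. A false prompt costs a review of one product and does not itself stop the trial.
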